#### Assessment Instruments

The survey includes the following self-reported questionnaires: the General Health Questionnaire - 12 items (GHQ-12) (31); the Depression, Anxiety and Stress Scale - 21 Items (DASS-21) (32); the Obsessive-Compulsive Inventory – Revised (OCI-R) (33); the Insomnia Severity Index (34); the Severity-of-Acute-Stress-Symptoms-Adult (35); the Suicidal Ideation Attributes Scale (SIDAS) (36); the Impact of Event Scale - 6 items (37); the UCLA loneliness scale - short version (38); the Brief COPE (39); the Post Traumatic Growth Inventory short form (40); the Connor-Davidson Resilience Scale – short form (41); the Multidimensional Scale of Perceived social support (42); the Pattern of Care Schedule (PCS)—modified version (43); the Maslach Burnout Inventory (only for health professionals) (44). Respondents’ main socio-demographic characteristics, as well as data on their Internet use, will be collected through an *ad hoc* schedule. All assessment instruments used for the study are detailed in **Table 1**.

**Table 1 T1:** Assessment tools used in the survey.

Assessment tool	Acronym	N. items	Description
General Health Questionnaire-12	GHQ-12	12	Each item assesses the severity of a mental problem on a 4-level Likert scale. The total score ranges from 0 to 36, with higher scores indicating worse conditions.
Depression, Anxiety and Stress Scale - 21	DASS-21	21	It consists of three subscales. The depression subscale assesses dysphoria, hopelessness, devaluation of life, self-deprecation, lack of interest/involvement, anhedonia, and inertia. The anxiety scale assesses autonomic arousal, skeletal muscle effects, situational anxiety, and subjective experience of anxious affect. The stress scale assesses difficulty in relaxing, nervous arousal, and being easily upset/agitated, irritable/over-reactive and impatient.
Obsessive-Compulsive Inventory – Revised	OCI-R	18	Each item assesses the severity of obsession or compulsion on a 5-level Likert scale. The total score range from 0 to 72, with higher scores indicating worse conditions.
Insomnia Severity Index	ISI	7	Each item assesses the nature, severity, and impact of insomnia on a 5-level Likert scale. The aspects evaluated includes sleep onset, sleep maintenance, and early morning awakening problems, sleep dissatisfaction, interference of sleep difficulties with daytime functioning, noticeability of sleep problems by others, and distress caused by the sleep difficulties. The total score ranges from 0 to 28.
Severity-of-Acute-Stress-Symptoms-Adult	SASS	9	It assesses the severity of post-traumatic stress disorder in adult individuals. Each item assesses the severity of post-traumatic symptoms during the past seven days.
Suicidal Ideation Attributes Scale	SIDAS	5	It assesses all the attributes of suicidal thoughts: frequency, controllability, closeness to attempt, level of distress associated with the thoughts, and impact on daily functioning. Each item is assessed on 10-level Likert scale. When the score at the first item is zero, the remaining items are not compiled.
Impact of Event Scale-6	IES-6	6	It assesses the impact of the traumatic event, including three subscales that describe the three major symptoms of posttraumatic stress: intrusion, avoidance, and hyperarousal.
UCLA loneliness scale - short version	UCLA	8	It is an 8-item scale designed to measure one’s subjective feelings of loneliness as well as feelings of social isolation.
Brief Coping Orientation to Problems Experienced	Brief-COPE	28	It includes 14 subscales designed for measuring effective and ineffective ways to cope with a stressful life event. The subscales include: self-distraction, active coping, denial, substance use, use of emotional support, use of instrumental support, behavioral disengagement, venting, positive reframing, planning, humor, acceptance, religion, and self-blame.
Post Traumatic Growth Inventory- short form	PTGI	10	It evaluates the construct of post-traumatic growth on a 6-level Likert scale.
Connor-Davidson Resilience Scale – short form	CD-RISC	10	It evaluates the levels of resilience and it includes the following five factors: personal competence, high standards, and tenacity; trust in one’s instincts, tolerance of negative affect, and strengthening effects of stress; positive acceptance of change and secure relationships; control; spiritual influences. Each item is rated on a 6-level Likert scale.
Multidimensional Scale of Perceived Social Support	MSPSS	12	It evaluates the levels of perceived adequacy of social support from the family, friends, and significant others on a 5-level Likert scale
Pattern of Care Schedule - modified version	PCS	20	It is an *ad hoc* schedule evaluating the pharmacological and nonpharmacological treatments received by participants
Maslach Burnout Inventory (only for healthcare professionals)	MBI	22	It evaluates the three dimensions of burnout: emotional exhaustion, depersonalization, and personal accomplishment

### Outcomes

#### Primary Outcome

The primary outcome of the study is the global score at the DASS-21. This choice is due to the fact that this assessment measure has already been used in a large population study carried out in China, thus giving us the opportunity to compare the Italian situation with the Chinese one (45). Our study hypothesis is that the pandemic and the related containment measures are associated with higher levels of depressive and anxiety symptoms in the surveyed population compared to a community Italian sample not exposed to the pandemic (46). Furthermore, a significant difference between groups will be identified (COVID-19 quarantine group = COVID-19 healthcare professional second-line < COVID-19+ group = COVID-19 healthcare professional first-line group < COVID-19 mental health group).

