### Data Analysis

Statistical analyses will be conducted according to a multistep plan. Missing data will be handled using the multiple imputation approach (47). Descriptive statistics will be calculated for the dependent and confounding variables. A bilateral alpha of 0.05 is considered, and error and confidence intervals are calculated at 95%.

The analytic plan will include: 1) data cleaning of the online dataset and replacement of missing values; 2) descriptive statistics of the general characteristics of the recruited sample, in terms of levels of depressive and anxiety symptoms, post-traumatic and stress-related symptoms, insomnia, satisfaction with life, suicidal ideation, hopelessness, post-traumatic growth, resilience, coping strategies, and social support; 3) sub-groups analyses based on the level of exposure to the pandemic (i.e., COVID-19 quarantine group vs. COVID-19+ patients group vs. COVID-19 healthcare staff group vs. COVID-19 mental health group); 4) calculation of a propensity score, in order to adjust our findings for the likelihood of being exposed to the pandemic and to the quarantine (48, 49). This method is adopted since it produces a better adjustment for differences at baseline, rather than simply including potential confounders in the multivariable models. The independent variables used for calculating the propensity score will include gender, age, socio-economic status, and geographical region. The obtained propensity score will be used to weight the observations in the multivariable analyses. In the final regression model, the inverse probability weights, based on the propensity score, will be applied in order to model for the independence between exposure to the pandemic/quarantine and mental health outcomes and estimation of causal effects (48, 49); 5) development of a Structural Equation Model (SEM), in order to evaluate the possible role as mediators and moderators of coping strategies, post-traumatic growth and usage of social networks on the severity of depressive and anxiety symptoms, post-traumatic and stress-related symptoms, suicidal ideation, and hopelessness.

In order to improve the external validity and generalizability of our findings, all analyses will be controlled for the impact of confounding variables, such as age, gender, and geographical region.

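### The primary outcome is the DASS-21 global score, but the hypothesis for the comparison with the unexposed community sample names only depressive and anxiety symptoms

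*Protocol article*

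**What the plan says.** Under Primary Outcome, the protocol article fixes the variable: "The primary outcome of the study is the global score at the DASS-21". The reason given is that "this assessment measure has already been used in a large population study carried out in China". The same paragraph then states the study hypothesis, that the pandemic and its containment measures go with "higher levels of depressive and anxiety symptoms in the surveyed population compared to a community Italian sample not exposed to the pandemic". A second hypothesis follows, an ordering between groups, which names no symptom domain.

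Table 1 (Assessment Instruments) says of the DASS-21: "It consists of three subscales". Depression and anxiety are described first. The third is distinct: "The stress scale assesses difficulty in relaxing, nervous arousal, and being easily upset/agitated, irritable/over-reactive and impatient".

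Data Analysis sets the test level ("A bilateral alpha of 0.05 is considered") but does not name the global score. Its steps 2 and 5 list depressive and anxiety symptoms apart from post-traumatic and stress-related ones. Step 2 also lists "insomnia, satisfaction with life, suicidal ideation, hopelessness, post-traumatic growth" among the characteristics to be described, and step 5 names hopelessness again as an outcome of the structural equation model. The Discussion words the expectation for the quarantine group differently, as a rise in all three of stress, anxiety and depression.

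**The concern.** The primary variable contains a component that the hypothesis leaves out. For the comparison with the community sample, a significant global score shows that the sum of three domains is higher. It does not show that depression or anxiety is higher. The reason given supports choosing the instrument, but not choosing its total over its subscales.

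This matters because the second aim of the study (end of the Background) is to identify which areas supportive interventions should target. If stress carried most of a difference, a conclusion worded as depression and anxiety would name the wrong domain.

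There is also a smaller inconsistency between the listed variables and the instruments. Assessment Instruments says that all tools are detailed in Table 1, yet none there measures satisfaction with life. Hopelessness appears there only as content of the DASS-21 depression subscale.

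**Working it through.** The protocol states no effect size, SD or power for the primary outcome, so there is no figure to reproduce. The check has two parts.

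**1. Setting the text side by side**

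| Place | Domains named |
|---|---|
| Primary Outcome, variable | DASS-21 total, i.e. depression + anxiety + stress (Table 1) |
| Primary Outcome, hypothesis against the community sample | depression, anxiety |
| Primary Outcome, ordering between groups | none |
| Data Analysis, steps 2 and 5 | depression and anxiety, with stress-related symptoms listed apart |
| Discussion, quarantine group | stress, anxiety, depression |

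The variable and the first hypothesis differ by one domain. No section says that a raised total must be confirmed on the depression and anxiety subscales.

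**2. How far stress alone could move the total (illustration)**

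From the document: more than 20,000 respondents expected (Discussion); two-sided alpha 0.05 (Data Analysis).

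Assumed: three subscales with equal SD (set to 1) and common pairwise correlation r; equal SDs in survey and reference sample; no weighting; reference sample of 400 or 1,000; stress higher by 0.3 SD, depression and anxiety unchanged.

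The variance of the total is 3 + 6r, so the shift in SDs of the total is 0.3/√(3 + 6r):

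- r = 0.6: 0.3/√6.6 = 0.117
- r = 0.7: 0.3/√7.2 = 0.112
- r = 0.8: 0.3/√7.8 = 0.107

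Standard error of the difference, with 20,000 respondents and a reference sample of 400: √(1/20,000 + 1/400) = 0.0505. The shift is therefore 0.107/0.0505 = 2.1 to 0.117/0.0505 = 2.3 standard errors.

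Power to declare the total higher, for r from 0.8 to 0.5:

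| Reference sample | Stress-only rise 0.3 SD | Stress-only rise 0.5 SD |
|---|---|---|
| 400 | 57% to 68% | 94% to 98% |
| 1,000 | 91% to 97% | about 100% |

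Tests of the depression and anxiety subscales would each reject only at the nominal 5% in this scenario.

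The total also cannot tell profiles apart. At r = 0.7, a rise of 0.1 SD in each subscale gives (0.1 + 0.1 + 0.1)/√7.2 = 0.112, the same shift as 0.3 SD in stress alone. Only the subscales separate the two.

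**The case against.** The strongest reply is that the hypothesis is loose shorthand. The Discussion names all three domains for the quarantine group, and two of the three summed subscales are the ones hypothesised. Data Analysis lists depressive and anxiety symptoms apart from stress-related ones, so a pattern driven by stress would probably be seen in the descriptive results. This largely stands as to intent. It does not remove the mismatch, because no section makes the conclusion on the community comparison depend on the subscales.

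A reader might go further and infer that a rise in stress alone would be reported as more depression and anxiety. The document does not say so; it could happen, and no more can be claimed. Nor does it say that confinement acts mainly on stress. The Background links quarantine to frustration, loneliness and worry as risk factors for anxiety and affective disorders among others, which are close to the hypothesised domains.

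The arithmetic also rests on an extreme case: a stress-only rise despite strongly correlated subscales, and a reference sample of unknown size. One could divide the shift by the standard error of the survey mean alone (1/√20,000 = 0.0071) and get 15 to 17. That treats the community sample as free of error, and mostly reflects the number of respondents.

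A reader might also conclude that no significant primary result could support the hypotheses. That is too broad, since the ordering between groups names no domain and fits a global score.

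**Conclusion.** The mismatch is real and confined to the comparison with the unexposed community sample. A higher DASS-21 global score would not by itself establish higher depressive and anxiety symptoms, and the text leaves room for that reading. The 0.11 to 0.12 SD, about 2 standard errors against a reference sample of 400, shows only that the misreading is possible at this study's size. It depends on the assumed equal variances, correlations of 0.6 to 0.8, a stress-only rise of 0.3 SD and the reference size. It is not a forecast. A difference driven mainly, rather than wholly, by stress raises the same problem.

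The variable list is a separate and minor matter. Satisfaction with life appears only in the descriptive step 2, so no model depends on it. Hopelessness can be produced from depression items, but as described it overlaps an outcome already in the model.

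**What to change.** - Keep the global score as the primary outcome. Restate the hypothesis against the community sample as overall distress (depression, anxiety and stress), in line with the Discussion.
- Allow a conclusion about depression or anxiety only from the corresponding subscale comparison with the community sample. If either subscale alone may support a claim, apply Holm: the smaller p-value against 0.025, then the larger against 0.05. If both must be higher, test each at 0.05 without adjustment.
- Leave the ordering hypothesis as it is.
- Drop satisfaction with life from step 2 or name its measure. Do not model hopelessness as an outcome distinct from depressive symptoms unless a separate measure is named.

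The cost is wording and two further comparisons on data already collected. The community sample must report the subscales; the article does not say whether it does. Replacing the global score by the two subscales as primary is less attractive: the Discussion reports that the 10,000 target was reached in 7 days, so the primary outcome would change during data collection.

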### Data Collection

#### Recruitment Procedure

An online survey has been set up through EUSurvey, a web platform launched in 2013 by the European Commission. The application, hosted at the Department for digital services (DG DIGIT) of the European Commission, is available to all EU citizens at https://ec.europa.eu/eusurvey. The survey will be online from March 30 to June 30, 2020 (https://ec.europa.eu/eusurvey/runner/COVIDSurvey2020). The survey takes approximately 15–30 min to be completed. Participants can stop the survey at any time and save their answers as “draft” on the web-platform. Furthermore, participants can interact with the principal investigator of the study and with all researchers through email messages at any time during and after study participation.

Participants will be subdivided into four groups: a) Group 1—COVID-19 quarantine group. This group includes the general population which are quarantined but not isolated, i.e., those not directly exposed to contagion nor in contact with COVID-19+ individuals; b) Group 2—COVID-19+ group, which includes isolated people directly/indirectly exposed to the virus; c) Group 3—COVID-19 healthcare staff group, which includes first- and second-line healthcare professionals; d) Group 4—COVID-19 mental health, which includes users of mental health services and all those who had already been diagnosed with a mental disorder.

The survey addresses the Italian population aged over 18 years through a multistep procedure: 1) email invitation to health professionals and their patients; 2) dissemination of the link through social media channels (Facebook, Twitter, Instagram) and the mailing lists of national psychiatric associations; 3) involvement of national associations of stakeholders (e.g., associations of users/carers); 4) official communication channels (e.g., university websites; websites of the hospitals directly involved in the management of the pandemic).

The invitation letter includes information on study purposes and confidentiality. The provision of the informed consent is mandatory in order to start the survey.

The snowball sampling procedure—without the definition of strict inclusion/exclusion criteria (except that of age limit)—will give us the opportunity to recruit a large sample of the Italian population and to evaluate the effect of the studied variables on the outcome measures.

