Another possible limitation of our study is the choice to use a web-based online survey, which may have limited the participation of people not having access to the Internet or not familiar with online tools, particularly the elderly. The cross-sectional design of the study does not allow an evaluation of changes over time as regards the levels of severity of symptoms. However, in order to overcome this possible bias, we will compare our findings with those already available from the Italian population (46) and will adopt a propensity score approach in order to understand the impact of the duration of exposure to the pandemic on the risk of developing psychiatric symptoms. With this methodology, we will be able to evaluate the levels of post-traumatic growth and the type of resilience styles in the study population in order to identify possible critical areas to be targeted in the post-acute phase. However, these psychological constructs are slow to change, and this is why we will promote a second wave of the survey, which will start six months after the end of the “lockdown phase” in Italy. Finally, the survey link can be used multiple times in order to allow sharing and re-posting it. This methodological choice could bias the findings, since the same person can potentially compile the survey several times. However, this methodological choice was due to the adoption of the “snowball” sampling, and it is rather unlikely that someone can compile the same long survey more than once.

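### The pandemic hypothesis sets the whole survey, which includes a mental health group by design, against an external community sample, and no named adjustment covers psychiatric case mix

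*Protocol article*

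**What the plan says.** Under Primary Outcome: "The primary outcome of the study is the global score at the DASS-21". The hypothesis is that the pandemic is associated with "higher levels of depressive and anxiety symptoms in the surveyed population compared to a community Italian sample not exposed to the pandemic". No subgroup is named on the survey side. The same section then orders the groups on the outcome, ending in "COVID-19 healthcare professional first-line group < COVID-19 mental health group".

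Under Recruitment Procedure, Group 4 is defined as "users of mental health services and all those who had already been diagnosed with a mental disorder", and Group 3 is healthcare staff. Sampling is by snowball, with age as the only criterion. The routes include "email invitation to health professionals and their patients", "the mailing lists of national psychiatric associations" and "involvement of national associations of stakeholders (e.g., associations of users/carers"), and also general social media and university and hospital websites. No share by route is given.

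Under Data Analysis, a propensity score built from gender, age, socio-economic status and region models the likelihood of exposure to the pandemic and quarantine, and supplies inverse probability weights. A closing sentence says that all analyses are controlled for confounders, with age, gender and region as examples.

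The limitations part of the Discussion concedes that a cross-sectional design cannot show change, and continues: "in order to overcome this possible bias, we will compare our findings with those already available from the Italian population". The same sentence adds the propensity score approach, there tied to duration of exposure.

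**The concern.** This is the only contrast in the article between Italians exposed to the pandemic and Italians who were not, so the first study aim rests on it. One side is a general community sample. The other contains a group defined by prior mental disorder, which the protocol itself expects to have the highest scores. If that group is a larger share of the survey than of the reference sample, the survey mean is higher even if no individual's symptoms changed. A larger survey does not reduce this bias; it only narrows the interval around a shifted value. The result would then be read as a pandemic effect and used to plan interventions.

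**Working it through.** **1. Does any stated device remove the difference in composition?**

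- The subgroup step compares respondents with each other. The reference sample does not enter it.
- The propensity weights model exposure to the pandemic or quarantine. The reference sample is external and unexposed, and the weights are not described as modelling membership of one sample or the other. Their four variables do not include psychiatric history or occupation.
- The general covariate sentence covers age, gender and region. It is open-ended, but it names neither psychiatric history nor healthcare work, and does not say how it would apply to an external sample.

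As described, none of them deals with psychiatric case mix in the external comparison.

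**2. The plan's own figure.** The Discussion gives an ideal target of 10,000 respondents and expects more than 20,000. No calculation is attached, so there is nothing to reproduce. I use N = 20,000 as an input.

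**3. Assumed inputs (not in the documents).** Excess share of Group 4 in the survey over the reference sample: 5 to 20 percentage points. Elevation d of Group 4 over the other respondents: 0.8 to 1.2 SD. Reference sample size m: 400, with 1,000 and 2,000 as alternatives. SD = 1 in both samples; true pandemic effect = 0.

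**4. Shift in the survey mean** = excess share × d.

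- Low: 0.05 × 0.8 = 0.04 SD
- High: 0.20 × 1.2 = 0.24 SD

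**5. Standard error of the difference** = √(1/N + 1/m).

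- m = 400: √(1/20,000 + 1/400) = 0.0505 SD
- Low: 0.04 / 0.0505 = 0.8 SE
- High: 0.24 / 0.0505 = 4.8 SE

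**6. Chance of a significant result in the 'higher' direction with no pandemic effect** (two-sided 5%, normal approximation, d = 0.8, N = 20,000):

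| Excess share | Shift (SD) | m = 400 | m = 1,000 | m = 2,000 |
|---|---|---|---|---|
| 5% | 0.04 | 12% | 23% | 40% |
| 10% | 0.08 | 35% | 70% | 93% |
| 15% | 0.12 | 66% | 96% | >99% |
| 20% | 0.16 | 89% | >99% | >99% |

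At N = 10,000 and m = 400 the figures are almost the same (12%, 35%, 65%, 88%), because the reference sample dominates the error.

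**7. After alignment.** If the excess share is brought to 0, the case-mix shift is 0 and the chance falls to the nominal 2.5%. This concerns measured case mix only.

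**The case against.** Four points can be made for the plan.

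- **It is a condensed article.** The mechanics of weighting to an external sample may stand in a full protocol or analysis plan that is not shown. This is fair, and the missing detail is not the point. What remains is printed here: the contrast is fixed on the whole survey, and the comparison is offered as a remedy for the cross-sectional design.
- **Age, gender and region are covered.** A reader might infer that nothing at all aligns the samples. The sentence on controlling all analyses contradicts that for these variables, at least in intention. The gap is psychiatric history and healthcare work.
- **Recruitment was not shown to be mainly psychiatric.** A reader might infer from the list of routes that the survey was filled largely through mental health channels. The documents give no shares. Social media and institutional websites are also used, the invited patients are not said to be psychiatric patients, and association mailing lists may reach professionals rather than service users. Only the user and carer associations point clearly to Group 4.
- **Results are also analysed by group.** The Discussion states the expected increase for the quarantine group separately, so a pooled mean driven by Group 4 would be partly visible. This limits the harm, but does not change the population on which the hypothesis is stated. For Group 3 the case is weaker still: second-line staff are expected to equal the quarantine group, so only first-line staff would raise the mean, by an unstated amount.

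The Discussion also admits self-selection and plans a second wave. The wave may inform later change, but supplies no pre-pandemic baseline.

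**Conclusion.** The point holds in a limited form. The external comparison pools Group 4 with everyone else, and no named adjustment covers psychiatric history or healthcare work, so case mix alone could produce the hypothesised result. The statement that the comparison serves to overcome the cross-sectional limitation is not supported.

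The size is unknown. Under the assumptions above the spurious shift is 0.04 to 0.24 SD, or about 0.8 to 4.8 SE with 400 reference subjects. At the low end it would usually go unnoticed; at the high end it would almost always be declared significant.

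Two stronger readings should be avoided. One could divide the shift by the survey's standard error alone (1/√20,000 = 0.0071 SD) and report about 6 to 34 SE. That treats the reference mean as known without error, which a published sample mean is not. Nor do the documents show that a positive result would be an artefact: a real pandemic effect may exist as well, and this design as worded cannot separate the two.

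**What to change.** Do not base the external comparison on the pooled, unweighted survey. Use one or both of these:

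- **Group 1 only** (no prior mental disorder), standardised to the reference sample's age, sex and, where reported, region.
- **The full sample**, reweighted to the reference sample's shares with a pre-existing mental disorder and in healthcare work, or to national shares if the reference does not report them. National shares align the survey with the country, not strictly with the reference sample, and this should be stated.

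Include the reference sample's own standard error in the interval. State that the Group 1 analysis deals with psychiatric case mix only. People drawn to the topic may score higher within Group 1 too, so it is not a conservative bound for all biases. Group 1 also leaves out people exposed to the virus, so it answers a narrower question.

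Word the result as an association. In the Discussion, replace the claim that the comparison overcomes the limitation with a statement that it gives context and remains open to differences in composition and self-selection.

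No new data collection is needed: the survey already records group membership and socio-demographic data. The cost is some weighting, a small loss of precision, and possibly a smaller headline difference. How far the standardisation can go depends on what the reference sample reports.

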## Discussion

Our survey will give us the opportunity to describe the impact of the pandemic on the mental health of different subgroups of the Italian population.

In fact, the analyses will be run according to the four subgroups of respondents: the general population not directly affected by the virus (COVID-19 quarantine group); people who have had a direct or indirect contact with the virus (COVID-19+ patients group); those working in health care units as first or second-line staff (COVID-19 healthcare staff group); people with mental health problems, independently from the contact with the virus (COVID-19 mental health). This choice is due to the evidence that stress and traumas have a different impact on different target groups (7, 50–52).

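### The primary-outcome hypothesis orders five groups, but the stated comparison has four with first- and second-line staff pooled, so it cannot test that ordering

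*Protocol article*

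**What the plan says.** The Primary Outcome section of the protocol article fixes the endpoint: "The primary outcome of the study is the global score at the DASS-21". After the main hypothesis, which compares the surveyed population with an unexposed Italian community sample, it adds that "a significant difference between groups will be identified" and gives the expected pattern: "COVID-19 quarantine group = COVID-19 healthcare professional second-line < COVID-19+ group = COVID-19 healthcare professional first-line group < COVID-19 mental health group". That is five groups in three tiers, with two equalities and two strict steps.

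Recruitment Procedure defines only four groups. The third is the "COVID-19 healthcare staff group, which includes first- and second-line healthcare professionals". Step 3 of Data Analysis compares "COVID-19 quarantine group vs. COVID-19+ patients group vs. COVID-19 healthcare staff group vs. COVID-19 mental health group", and the Discussion repeats that "the analyses will be run according to the four subgroups of respondents".

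Secondary Outcomes does contrast first-line with second-line staff, but only on mental exhaustion and suicidal ideation. On error rates, Data Analysis says "A bilateral alpha of 0.05 is considered" and plans 95% intervals. It names no specific test for the group comparison.

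**The concern.** The hypothesis puts the two staff lines in different tiers, while the analysis described for it puts them in one group. An analyst who follows step 3 faithfully will report one staff mean, and the hypothesis makes no direct statement about that mean. The between-group part of the primary hypothesis could then be neither supported nor contradicted as written.

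The equality signs raise a second difficulty. The only language attached to the pattern is that of significant difference. A non-significant difference is not evidence of equality, and in a very large survey a difference too small to matter can be significant. The reading of each equality would then depend on how many people happened to fall in each group.

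**Working it through.** **Plan's own figures.** The Discussion gives a target of 10,000 and an expectation of more than 20,000, without an effect size, SD, power or group shares. There is nothing to reproduce. The only stated statistical inputs are alpha 0.05 two-sided and 95% intervals.

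**1. What four groups can and cannot test.** Write Q (quarantine), S (second-line), C (COVID-19+), F (first-line), M (mental health). Five groups give 10 pairs. Three involve no staff: Q–C, C–M and Q–M. These remain testable. The other seven involve S or F: the two equalities (S = Q, F = C) and five strict relations (S < C, Q < F, S < F, S < M, F < M). None of the seven is tested by a pooled staff group.

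**2. Why the pooled mean is uninformative.** Set the lower tier at 0 and the middle tier at D (in SD units), with f the first-line share of staff. Under the hypothesis the pooled staff mean is (1 − f)·0 + f·D = fD, which is fD above Q and (1 − f)D below C. Take D = 0.2 and f = 0.5 (assumed):

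- Hypothesis true (S = 0, F = 0.2): pooled mean 0.10.
- Both equalities false (S = F = 0.10): pooled mean 0.10.
- Staff lines reversed (S = 0.2, F = 0): pooled mean 0.10.

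The three cases give the same four group means.

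**3. What the four-group output would tend to show if the hypothesis is true.** SE = √(1/n₁ + 1/n₂) in SD units; power ≈ Φ(difference/SE − 1.96). Assumed: N = 20,000, D = 0.2, f = 0.5, and three sets of group shares.

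| Shares Q/C/staff/M | n: Q, C, staff | staff vs Q significant | staff vs C significant |
|---|---|---|---|
| 25/25/25/25% | 5,000, 5,000, 5,000 | 0.999 | 0.999 |
| 70/5/15/10% | 14,000, 1,000, 3,000 | 0.999 | 0.782 |
| 80/3/12/5% | 16,000, 600, 2,400 | 0.995 | 0.591 |

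Middle row, staff vs C: SE = √(1/3,000 + 1/1,000) = 0.0365; 0.10/0.0365 = 2.74; Φ(0.78) = 0.78. The output tends towards Q < staff < C, with neither equality visible. Over D = 0.1 to 0.3 and f = 0.3 to 0.7, the probabilities run from 0.28 to 1.00 (staff vs Q) and from 0.10 to 1.00 (staff vs C), so the figures depend heavily on the assumptions.

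**4. The equalities once staff are split.**

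- Two true equalities, each tested at 0.05 and sharing no group: P(at least one rejected) = 1 − 0.95² = 9.75%.
- Small gap, Q vs S, with N = 20,000 and f = 0.3 to 0.7 over the three sets of shares: a 0.05 SD gap is significant with probability 0.26 to 0.62, and a 0.1 SD gap with probability 0.75 to 0.995. Example, 14,000 vs 1,500: SE = 0.0272; 0.1/0.0272 = 3.68; Φ(1.72) = 0.957.
- Smallest difference detectable with 80% power, C vs F: 2.80 × SE = 0.06 to 0.16 SD. Gaps below that would often be non-significant without being zero.

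**5. Could the equalities be supported by a margin?** Probability that the 95% interval lies inside ±m when the true difference is 0: 2Φ(m/SE − 1.96) − 1, with N = 20,000 and f = 0.5.

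| Margin (assumed) | Q vs S | C vs F |
|---|---|---|
| 0.2 SD | 1.00 | 0.96 to 1.00 |
| 0.1 SD | 0.83 to 0.97 | 0.03 to 0.97 |

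Example, C vs F with 1,000 vs 1,500: SE = 0.0408; m = 0.2 gives 2Φ(2.94) − 1 = 0.997; m = 0.1 gives 2Φ(0.49) − 1 = 0.38.

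**The case against.** The strongest reply is that the bracketed pattern only sketches an expectation. The main study hypothesis is the comparison with an unexposed community sample, which this point does not touch. Secondary Outcomes already separates the two staff lines, so the authors evidently mean to have that variable. Margins, contrasts and multiplicity rules commonly sit in an analysis plan that is not shown, and reading the equality signs as formal equivalence claims is an interpretation.

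Much of this stands. The absence of a margin is not by itself a fault here, and equivalence testing is not the only remedy. What does not fall away is the conflict in the text: an ordering that separates the staff lines on the primary outcome, against an analysis stated twice as having four groups. An analysis plan written faithfully from Data Analysis would inherit that conflict.

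Two stronger readings are tempting, and the document does not support them:

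- A reader might infer that pooling would make the study refute its own hypothesis when it is true. It would not. A pooled staff mean between the tiers is what the hypothesis predicts, and the protocol nowhere says that pooled staff equal either group. The result would count as a refutation only if misread.
- A reader might infer that the plan could never support the equalities. That is true of a difference test taken alone. But 0.05 is given as a general alpha, no test is named for step 3, and the planned 95% intervals could support equality against a margin set in advance.

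**Conclusion.** The point holds as an internal mismatch on the primary outcome. The five-group ordering cannot be tested by the four-group comparison, which leaves 7 of the 10 pairwise relations, including both equalities, unexamined. This conclusion needs no numerical assumption. The comparisons among the quarantine, COVID-19+ and mental health groups are unaffected, as is the main hypothesis against the community sample.

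The further point, that non-significance does not show equality and that trivial gaps may be significant, is sound in principle. Its size is conditional: every power figure above rests on assumed group shares, first-line share, tier gap and margin, because the document gives only total numbers. The matter should be corrected, but it is a repair of wording and not a flaw in the data to be collected.

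**What to change.** - In step 3 of Data Analysis, and in the matching sentence of the Discussion, state that for DASS-21 the healthcare staff group is split into first- and second-line, giving five groups.
- Name the contrasts that test the strict steps in advance.
- For the two equalities, choose one of two routes. Either judge the confidence interval against a margin in DASS-21 units, fixed before the data are examined, or restate them as no difference expected and limit confirmatory claims to the strict contrasts.
- If a margin is used, keep the interval's confidence level consistent with any multiplicity control. For example, Holm over four contrasts starts at 0.05/4 = 0.0125, which for two one-sided tests corresponds to a 97.5% interval, not a 90% one. The probabilities in part 5 of the working are for unadjusted 95% intervals.

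The cost is wording and smaller staff subgroups. With a tight margin and a small COVID-19+ group, the second equality may be out of reach (0.03 in the least favourable case above), which would favour restating it. The repair assumes that each respondent's staff line is recorded, as the planned secondary comparison implies but the document does not state outright.
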